### 2.5. Study Procedures

After providing informed consent, participants will undergo full-mouth periodontal treatment (approximately less than 30 min in the supine position without a rubber dam under High-Capacity Dental Suction conditions) in two different sessions. During the first session, full-mouth periodontal treatment will be performed without the use of a nasal cannula or other respiratory devices. Participants will subsequently complete a self-administered questionnaire. In the pre–post, fixed-sequence, within-subject feasibility design, stress during the second session may decrease independently of the HFNC due to factors such as habituation, reduced treatment volume/invasiveness, and changes in psychological adaptation. Therefore, the following points will be carefully considered. The two sessions will be conducted and standardized at the same time of day, by the same operator with five years of clinical experience using same instrumentation type with consistent treatment extent and duration, and each session involves the treatment of only one side of the jaw or one quadrant within the full-mouth periodontal treatment area in a total of two sessions. In addition, to minimize the possibility of marked changes in periodontal status by the second session, the interval between the two sessions will be limited to within four weeks.

The second full-mouth periodontal treatment session will be scheduled for at least four weeks after the first session. During this session, full-mouth periodontal treatment will be performed with a dedicated HFNC (AIRVO3, Fisher & Paykel Healthcare Ltd., Auckland, New Zealand). Prior to the start of treatment, the nasal cannula will be inserted into both nostrils, and warmed and humidified air will be delivered at an initial flow rate of 20 L/min. If no discomfort is reported, the flow rate will be gradually increased to a maximum of 30 L/min. The AIRVO3 HFNC will be applied with fixed FiO_2_ at 0.21 at a temperature of 37 °C, with appropriate matched cannula size (S, M, L size) for all patients and criteria for flow escalation and discontinuation.

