No waveform correction will be performed during measurements using either the MWM20 EEG or ECG monitor. In the dental treatment setting, swallowing, mandibular movements, instrument noise, and body motion may also further interfere with EEG α-wave recordings. Therefore, the protocol restricts measurements to standardized short resting periods (an approximately two-minute resting state) for stable measurement before and after treatment rather than during instrumentation itself. It should be noted that the minimum valid recording length required for EEG α-wave analysis will be maintained for at least two minutes, with no large spikes in waves. All the participants must avoid swallowing saliva, opening or closing the mouth, and body movement during the measurement. In EEG (electroencephalogram) data, sections with noise may show large spikes in delta waves. In EEG data, sections with noise may show large spikes in EEG waves.

This is primarily believed to be caused by significant electromyographic activity, such as body movements or blinking. In MW2, data is output using 4 s windows shifted by 2 s.

This is then averaged over 10 s and exported as a CSV file. Since the numerical values in noisy sections change significantly for only an instant, removing those sections afterward serves as a method to address noise and artifacts. The EEG α-wave activity will be expressed as a mean appearance rate during a predefined resting window. In this feasibility study, the evaluation of EEG α-wave analysis would be a highly exploratory feasible measure.

The baseline value will be established prior to the intervention, and signal analysis will be performed using automated analysis with MemCalc™.

The protocol will be stopped if a significant risk to the research subjects or extreme discomfort is identified. For example, if patients experience adverse events such as epistaxis, discomfort, aspiration/cough events, or desaturation according to vital sign monitoring, the principal investigator should adjudicate the AEs and should stop the protocol.

In this study, safety and infection control in the dental operatory require explicit handling. HFNC therapy introduces airflow, humidification, and interface equipment in a setting with aerosols and cross-infection risk. We will use a single-use circuit and cannula with a built-in filter device. After completion of each session, the AIRVO3 machine will be decontaminated using a special cleaning circuit.

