As with conventional hypoxic therapy interventions, there are concerns about the occurrence of adverse events—such as a decrease in SpO_2_—for which a causal relationship cannot be ruled out. According to past reports, the majority of these adverse events are mild to moderate in severity, and studies have shown that they can be rapidly resolved through airway management techniques and control of the depth of sedation. The AIRVO3 device allows for confirmation of SpO_2_ sensor attachment and respiratory rate during monitoring, and an alarm can be set to sound when the SpO_2_ level falls below 90%.

The principal investigator (PI), as the person responsible for evaluation, will ensure that appropriate interventions are implemented for any adverse events of concern. It has been noted that high-flow nasal cannulation may generate aerosols when the flow rate exceeds the patient’s tidal volume, and the use of surgical masks, goggles, and rubber gloves is mandatory during the procedure to prevent operator infection. These measures have been proven effective in preventing aerosol-transmitted infection during the COVID-19 pandemic.

A questionnaire survey will score dental treatment comfort using a 5-point scale across 9 items (1: Not at all, 2: Slightly, 3: Somewhat, 4: Quite a lot, 5: Very much). (File S1)

Q1:Did your body tense up during treatment?Q2:Did your breathing become faster during treatment?Q3:Did you sweat during treatment?Q4:Did you feel nauseous or experience vomiting during treatment?Q5:Did your heartbeat quicken during treatment?Q6:Was it easy to breathe through your nose during treatment?Q7:Were you able to swallow saliva or water residue effectively during treatment?Q8:Did you feel anxious during treatment?Q9:If you were to use it again, which method would you prefer: the first or second?

For Q1~Q8, the Likert scale will be administered in numerical order.

Q9 (Nominal scale: preference) will be administered only after the second session and will be used as a distinct nominal item.

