### 2.6. Outcomes (Table 1)

#### 2.6.1. Primary Feasibility Outcomes

The primary feasibility outcomes are as follows:Recruitment ≥ 5/month (30 cases/6 months);Retention rates ≥ 70%;Patient tolerance and acceptability of the HFNC during dental treatment ≥ 80%;Completeness of physiological and questionnaire-based data collection ≥ 80%;Occurrence of device-related adverse events at less than 5% (less than one case).

**Table 1 dentistry-14-00208-t001:** Outcomes table.

Category	Outcome	Purpose
Primary (Feasibility)	Recruitment, retention	Trial feasibility
	Acceptability, tolerance	Practical implementation
	Data completeness	Outcome feasibility
	Adverse events	Safety
Secondary (Exploratory)	Pulse rate, respiratory rate	Stress physiology
	HRV (LF/HF)	Autonomic response
	EEG alpha activity	Neurophysiological stress
	Questionnaire	Patient-centered outcomes

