#### 2.6.3. Statistical Analysis

As this is a pilot feasibility study, formal hypothesis testing is not planned. Feasibility and exploratory outcomes will be summarized descriptively. Analyses of secondary outcomes will be exploratory and intended to inform the design of future definitive trials. Regarding continuous outcomes, we will estimate the mean difference between treatment with a HFNC and treatment without a HFNC, along with its 95% confidence interval.

In the case of missing data, the proportion of missing values will be reported for each variable at each time point. Summary statistics will be calculated excluding missing values. Differences between time points will be assessed after excluding subjects with missing values, as this study will include only two time points.

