#### 2.6.4. Sample Size

As this is a pilot feasibility study, a formal sample size calculation based on statistical power was not performed. Approximately 30 patients per year who meet the eligibility criteria are treated at the Department of Special Care Dentistry of Nagasaki University Hospital. Therefore, a target sample size of 30 participants was considered feasible within the planned study period and sufficient to assess feasibility outcomes, including recruitment, acceptability, data completeness, and safety, to inform the design of future definitive trials.

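### The rule to exclude missing values does not suit the primary HFNC acceptability criterion (≥ 80%), because HFNC-related withdrawals and unanswered items after a stop drop out instead of counting as failures

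*Protocol article*

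**What the plan says.** All places are in the protocol article.

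- Section 2.6.1 lists the primary feasibility marks. Among them are "Patient tolerance and acceptability of the HFNC during dental treatment ≥ 80" per cent and "Retention rates ≥ 70" per cent. Neither has a stated denominator.
- Section 2.5 gives HFNC in the second session only: "During the first session, full-mouth periodontal treatment will be performed without the use of a nasal cannula or other respiratory devices". Consent comes before both sessions.
- Section 2.5 also covers adverse events during treatment, with discomfort among the examples: "the principal investigator should adjudicate the AEs and should stop the protocol". It does not say how a stopped participant counts towards tolerance, acceptability or retention.
- The preference item of the questionnaire (Q9) "will be administered only after the second session".
- Section 2.6.3 says that feasibility and exploratory outcomes alike will be summarised descriptively. It promises the proportion missing for each variable at each time point, then states: "Summary statistics will be calculated excluding missing values". Feasibility outcomes are not exempted.
- Section 2.6.4 sets the size: "a target sample size of 30 participants was considered feasible within the planned study period".

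**The concern.** For most variables, leaving out missing values is an ordinary descriptive choice. For this criterion the absence of a value can itself be the failure being measured. A participant who has had session 1 and then declines the HFNC session because of HFNC has shown non-acceptance, but has no session 2 record. A participant taken off HFNC before the acceptability question is put has shown intolerance, but may have no acceptability answer. The stated rule removes both from the acceptability rate. The Limitations section explains that the session without HFNC comes first to limit anxiety about the device, so the sponsor itself regards some reluctance as possible.

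The Discussion treats tolerance and acceptability as prerequisites for a definitive trial. A rate calculated only on those willing to have HFNC and able to answer afterwards would overstate how acceptable it is to the patients such a trial would enrol.

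**Working it through.** **Inputs.** Enrolled N = 30 (2.6.4). Recruitment mark "Recruitment ≥ 5/month (30 cases/6 months") (2.6.1). Retention mark 70% and tolerance/acceptability mark 80% (2.6.1). The document gives no expected dropout, tolerance rate or stop rate, so the counts below are illustrations.

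**The plan's own figure.** 5 per month × 6 months = 30. This agrees with the target of 30.

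**Step 1: how many reach HFNC.** The fewest retained that still pass is 0.70 × 30 = 21, so up to 9 of 30 may be lost with the retention mark met.

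**Step 2: effect of a stop without an acceptability answer.** Let a = number accepting, n = number attending session 2, s = number stopped without answering. The exclusion rule gives a/(n − s). Scoring those stops as failures gives a/n.

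| n | a | s | Excluded | Scored as failure |
|---|---|---|---|---|
| 21 | 16 | 1 | 16/20 = 80.0% (met) | 16/21 = 76.2% (not met) |
| 21 | 15 | 6 | 15/15 = 100% (met) | 15/21 = 71.4% (not met) |

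The second row is an extreme case. It shows that dropping stops pushes the rate towards 100%.

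**Step 3: effect of HFNC-related withdrawal before session 2.** Let w = number who withdraw for that reason. Excluding them gives a/n. Counting them as non-acceptance gives a/(n + w).

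- n = 21, a = 17: w = 0 gives 17/21 = 81.0% (met). w = 1 gives 17/22 = 77.3% (not met).
- n = 21, a = 21: w = 5 gives 21/26 = 80.8% (met). w = 6 gives 21/27 = 77.8% (not met).

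The outcome therefore depends on the reason for non-return as well as on how many do not return. Non-return unrelated to HFNC (w = 0) leaves the rate among attenders unchanged.

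**Step 4: attenders beside enrolled.** With r attending, the fewest tolerating that meet 80% of attenders, and the same number over 30:

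| Attending r | Fewest tolerating | Of attenders | Of 30 enrolled |
|---|---|---|---|
| 21 | 17 | 81.0% | 56.7% |
| 24 | 20 | 83.3% | 66.7% |
| 27 | 22 | 81.5% | 73.3% |
| 30 | 24 | 80.0% | 80.0% |

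Meeting 80% of all enrolled takes 24/30. For r from 21 to 28 (2 to 9 lost) some counts meet the mark on attenders and miss it on enrolled. At r = 29 the requirement is 24 either way (24/29 = 82.8%, 24/30 = 80.0%). At r = 21 even 21/21 is only 21/30 = 70.0%, so an all-enrolled criterion of 80% could not be met at a retention level the plan accepts.

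**The case against.** The strongest reply is that attenders are the natural denominator. The criterion concerns HFNC during treatment, only someone treated with HFNC can show tolerance, and non-return has its own primary mark. Counting every non-returner against both marks would make the 70% mark redundant, and would bias the rate downward where non-return has nothing to do with HFNC. This stands. A reader might infer from 17/21 against 17/30 that the criterion should be judged on all enrolled, or that its verdict is wrong at 70% retention. The document supports neither.

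The loss is also visible: retention and the proportion missing for each variable will be reported, so x/30 could largely be worked out. This stands too, but the 80% mark itself would still be read on the reduced group.

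A stop on HFNC is an observed tolerance result, and no section calls it missing. This holds for tolerance. It does not settle acceptability, which needs an answer that a stopped participant may not have given. Nor does any section make Q9 the acceptability measure: the questionnaire is listed as a secondary outcome, so the timing of Q9 alone does not show that primary acceptability is lost.

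Finally, denominators are often left to a fuller document, and the missing-data paragraph is partly worded around comparing two time points. An unstated denominator alone would indeed be no finding. Here, however, the article states a rule in the section that covers feasibility outcomes and exempts none of them. Applying it to a single-session proportion is its plain reading, though not one the text spells out.

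**Conclusion.** The point holds in a limited form. The available-case rule in 2.6.3 does not suit a primary threshold for which missingness can be the failure itself. It removes HFNC-related withdrawals, and participants stopped before answering, from the acceptability rate. The resulting bias is upward and of unknown size, because the document gives no basis for the number of such participants. Near the mark one participant can change the result (16/20 against 16/21; 17/21 against 17/22).

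This rests on three assumptions: that the rule applies to feasibility outcomes as written, that some participants withdraw because of HFNC or are stopped before answering, and that acceptability is taken from an answer given at or after session 2.

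Two stronger readings should not be drawn. Thirty per cent is the largest loss compatible with passing retention and no forecast of dropout. The document also sets marks to be described, without a formal progression rule, so it contains no go/no-go decision to be reversed. The comparison of 81.0% with 56.7% shows that the attender and enrolled rates need to be read together, and no more than that.

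**What to change.** In 2.6.1 and 2.6.3, exempt the tolerance/acceptability criterion from the exclusion of missing values and state its scoring:

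1. **Tolerance:** denominator, all who attend session 2 and are offered HFNC. Refusal, removal or any stop counts as not tolerated.
2. **Acceptability:** the same denominator, with refusal, removal, any stop, or an unanswered item after a stop counted as not acceptable. Participants who withdraw before session 2 for an HFNC-related reason are added to the denominator as non-acceptance.
3. **Beside the 80% criterion:** report the proportion of all enrolled who attended and tolerated HFNC (x/30), with reasons for non-return.

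This keeps attenders as the basis of the criterion and avoids the clash with the 70% retention mark that an all-enrolled criterion would create. It should be settled before data are seen. The cost is a few sentences, one reason-for-withdrawal field and a possibly less favourable rate. No extra participants or procedures are needed, and no treatment or stopping rule changes.

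### The primary safety criterion equates a rate below 5% with fewer than one case, but with 21 to 30 participants exposed a single case passes the percentage and fails the count

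*Protocol article*

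**What the plan says.** Section 2.6.1 lists five primary feasibility criteria. The safety criterion is "Occurrence of device-related adverse events at less than 5% (less than one case"). The bracketed words restate the percentage as a number of cases. Two other criteria in the list bear on it: "Retention rates ≥ 70" per cent, and "Patient tolerance and acceptability of the HFNC during dental treatment ≥ 80" per cent.

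Section 2.6.4 sets the sample size: "a target sample size of 30 participants was considered feasible within the planned study period and sufficient to assess feasibility outcomes". The device is used only in the second session, so each participant has at most one exposed session.

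On what counts as an event, section 2.5 says "The protocol will be stopped if a significant risk to the research subjects or extreme discomfort is identified". The next sentence gives examples, "if patients experience adverse events such as epistaxis, discomfort, aspiration/cough events, or desaturation according to vital sign monitoring", and asks the principal investigator to adjudicate the events and stop. Section 2.6.3 plans no formal hypothesis testing and treats feasibility outcomes descriptively.

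**The concern.** A count of fewer than one case can only be zero. A rate below 5% in about 30 people leaves room for one. If the two halves of the criterion are different rules, a trial with exactly one device-related event both meets and misses its only primary safety criterion, and whoever writes the report can choose the reading after the result is known. One event is a plausible outcome in a study of this size.

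The event definition adds to the uncertainty. Discomfort appears without a grade in one sentence of section 2.5 and as extreme in the sentence before, while the tolerance criterion accepts that some patients will not tolerate the device. It is therefore unclear which discomfort would use up an allowance of zero or one.

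**Working it through.** **Inputs.** Target of 30 participants (section 2.6.4). Retention floor of 70%, event threshold of 5% or fewer than one case, and tolerance floor of 80% (all section 2.6.1). The documents give no expected event rate and no confidence level for this criterion. The true rates and 95% levels below are assumptions.

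**1. Reproducing the plan's count.** 0.05 × 30 = 1.5 cases, so the largest whole number of cases below 5% is 1, since 1/30 = 3.3% and 2/30 = 6.7%. The stated count, "less than one case", allows 0. The count does not follow from the percentage.

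**2. Other denominators.** The retention floor gives 0.70 × 30 = 21. There, 0.05 × 21 = 1.05 and 1/21 = 4.8%, so one case still passes the percentage. In general 1/n < 0.05 requires n > 20. The percentage therefore allows exactly one case at every n from 21 to 30. At n = 20, 1/20 = 5.0%, one case fails both forms, and they agree. With 30 enrolled, 20 retained would be 66.7%, below the plan's own retention floor.

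**3. Effect of the choice with 30 exposed.** For a true rate p, the zero-case rule is met with probability (1 − p)^30. The at-most-one rule is met with probability (1 − p)^30 + 30p(1 − p)^29. At p = 0.02 these are 0.98^30 = 0.545 and 0.545 + 30 × 0.02 × 0.98^29 = 0.545 + 0.334 = 0.879.

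| Assumed true rate | Zero cases | At most one case |
|---|---|---|
| 1% | 74.0% | 96.4% |
| 2% | 54.5% | 87.9% |
| 3% | 40.1% | 77.3% |
| 5% | 21.5% | 55.4% |
| 10% | 4.2% | 18.4% |

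With 21 exposed and a true rate of 2%, the figures are 65.4% and 93.5%.

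**4. Discomfort, passages side by side.** The first stopping sentence in section 2.5 speaks of extreme discomfort. The second names discomfort with no grade as an adverse event. The tolerance criterion in section 2.6.1 is met with 24 of 30 (0.80 × 30 = 24), so six may fail to tolerate the device. Suppose one participant has discomfort that is adjudicated as a device-related event, and the other 29 tolerate the device. Tolerance is then at least 29/30 = 96.7% and passes, while safety fails under zero cases and passes under the percentage.

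**5. Precision of the observed rate.** Exact (Clopper-Pearson) two-sided 95% limits: for 0/30 the upper limit is 1 − 0.025^(1/30) = 11.6%; for 1/30 the interval is 0.1 to 17.2%; for 0/21 the upper limit is 16.1%.

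**The case against.** The best defence is that this is a bracketed gloss on one of five criteria in a descriptive pilot, and that the article attaches no explicit go/no-go rule to the thresholds. That limits the consequence. It does not remove the contradiction: both forms stand in the text of a primary criterion, and an analysis plan that is not shown cannot make both true.

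Three stronger readings are tempting, and the documents do not support them.

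- A reader might infer that mild discomfort is listed as an adverse event, or that any single cough or complaint fails the safety criterion. Section 2.5 gives discomfort no grade, and its only mention of mild severity concerns events in past reports. It pairs cough with aspiration, presents the list as examples following the sentence on significant risk or extreme discomfort, and has the principal investigator adjudicate. Section 2.6.1 counts only device-related events. What remains is an ambiguity about severity.
- A reader might infer that the plan errs by setting a rate that 30 patients cannot demonstrate. It is true that even 0/30 does not exclude 5%. But section 2.6.3 plans only description, section 2.6.4 disclaims a power basis, and the Limitations ask for caution. The words "sufficient to assess feasibility outcomes, including recruitment, acceptability, data completeness, and safety" do not claim proof of a true rate below 5%. This is a limit on interpretation.
- A reader might infer that 30 patients exclude event rates above roughly 10 to 12%. That holds only if no event occurs in all 30; one event, or fewer exposed, gives the wider limits shown above.

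Nor do the documents show which half of the criterion was meant. Zero may be intended as readily as at most one.

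**Conclusion.** The criterion is wrong as written and should be corrected before data are seen. The percentage allows one case and the count allows none at every denominator from 21 to 30, where one case is 3.3% to 4.8%. With 30 exposed and a true rate of 2%, the choice moves the chance of meeting the criterion from 55% to 88%; at 5% it moves it from 21.5% to 55.4%.

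The contradiction itself rests only on the plan's own figures. The range from 21 to 30 assumes that 30 are enrolled and retention is met; if so few are enrolled that 20 or fewer are exposed, the two forms coincide. The probabilities further assume independent participants, each counted once, and true rates chosen for illustration.

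The unclear status of discomfort is a second, smaller inconsistency that needs reconciling. The width of the interval is a point about reporting.

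**What to change.** 1. In section 2.6.1, keep one rule, chosen by the sponsor before data are seen, and state it as a count with its denominator, the participants in whom HFNC was started. It would read either as at most 1 case (below 5%) or as 0 cases. Delete the other form. If zero is meant, the matching percentage with 30 exposed is below 3.3%, not below 5%.
2. Reconcile the two stopping sentences in section 2.5 with each other and with the tolerance and safety criteria in section 2.6.1, so that it is clear which discomfort counts towards the safety criterion. That classification is the sponsor's to make.
3. As a secondary recommendation, report the observed adverse-event proportion with its exact 95% interval, and say that meeting the threshold describes the sample and does not show a true rate below 5%.

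The first change is one line and the second a few words in two sections. The third adds one interval to a table. None needs more patients or visits. The cost is that the sponsor must commit itself: zero cases makes failure fairly likely even for a device with a low event rate, while at most one passes more often if the true rate is high (18.4% against 4.2% at a true rate of 10% with 30 exposed).
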